### Outcomes

#### Primary Outcome: SMSE-PBP

The primary quantitative outcome is measured by the SMSE-PBP, encompassing 3 dimensions across 10 subscales with a total of 60 items, validated for reliability [24]. The SMSE-PBP spans prepregnancy (dimension 1) with a 3-factor scale of 13 items, pregnancy (dimension 2) with a 5-factor scale of 32 items, and hospital stay (dimension 3) with a 2-factor scale of 15 items [24]. This scale was selected due to the absence of existing measures for behaviors related to PBP and the critical role of self-efficacy in health behavior [25]. Responses are gauged on a 5-point Likert scale from 1=I can hardly do it to 5=I can do it very well, with the mean of the total item scores ranging from 1 to 5. Scores for prepregnancy, pregnancy, and hospital phases indicate respective levels of self-management self-efficacy, with higher scores reflecting greater efficacy. At the time of development, Cronbach α was reported as 0.88 for dimension 1, 0.96 for dimension 2, and 0.96 for dimension 3 [24].

#### Secondary Outcomes

##### Health Belief Model Scale for Premature Birth Prevention

This scale assesses perceived susceptibility, severity, benefits, and barriers regarding premature birth, featuring 4 dimensions across 15 subscales with 96 items, validated for reliability [26]. The number of items in the 4 dimensions of the HBM-PBP is as follows: perceived susceptibility (21 items), severity (26 items), benefits (27 items), and barriers (22 items).

Each item on this scale is rated using a 5-point Likert scale that ranges from 1=not likely at all to 5=very likely. The scores for each dimension are computed as the mean of the total item scores, ranging from 1 to 5. Higher scores across these dimensions indicate stronger health beliefs and perceptions concerning the susceptibility, severity, benefits, and barriers of premature birth. At the time these measures were developed, the Cronbach α values were established as 0.87 for perceived susceptibility, 0.94 for perceived severity, 0.94 for perceived benefits, and 0.92 for perceived barriers [26].

##### Premature Birth Prevention Intention

The PBPI score assesses participants’ intentions toward preventing premature birth. This instrument was specifically developed for this trial, drawing upon previous research on prevention intention. Participants respond to 3 statements: “I intend to do something to prevent premature birth,” “I plan to do something to prevent premature birth,” and “I will try to do something to prevent premature birth.” Responses are captured on a 7-point Likert scale from 7=strongly agree to 1=strongly disagree. The mean of the total item scores, ranging from 1 to 7, reflects the intensity of the participant’s prevention intention, with higher scores indicating stronger intentions toward preventing premature birth.

#### Feasibility Outcomes

##### Client Satisfaction Questionnaire-8

Participant satisfaction with the web-based education program will be measured using the CSQ-8, developed by Attkisson and Zwick [27], which consists of 8 items rated on a 1- to 4-point Likert scale; higher aggregate scores indicate greater satisfaction. Criterion validity was tested, and Cronbach α was reported as 0.93 [27].

##### Quality of the Website

The quality of the website used for the study will be assessed with a scale developed by Kang et al [28] and modified by Choi [29], featuring 20 items also rated on a 1- to 4-point Likert scale. A higher score on this scale reflects a more positive evaluation of the website’s quality by users. Content validity was evaluated by experts [28,29] and reported a Cronbach α of 0.82 [29].

##### Use of the Web-Based Intervention

In the experimental group, the use of the web-based intervention will be assessed based on the number of logins during the intervention period, the number of completed series to the end, the number of endings collected for each series, the user’s activities (reflections and comments), and messages to be left in the inquiry. The use of the intervention in the comparison group will be assessed based on users’ reflections on the educational program in the guestbook.

#### Qualitative Outcome

This study will gather qualitative insights using a semistructured interview to complement the quantitative data. The primary qualitative outcome will center on an open-ended question that explores participants’ perceived changes in self-efficacy for self-management of PBP before and after engaging with the education program. Secondary outcomes will delve into participants’ perceptions of susceptibility, severity, benefits, and barriers related to PBP, as framed by HBM-PBP, both pre- and postparticipation. Additionally, open-ended questions concerning satisfaction with the education program and the quality of the website will be posed to assess feasibility outcomes (Multimedia Appendix 2). Follow-up questions will be tailored based on participants’ initial responses to these open-ended inquiries.

#### Demographic Characteristics and Pregnancy- and Birth-Related Characteristics

Demographic characteristics encompass age, education level, occupation, marital status, monthly income, and area of residence. Additionally, pregnancy- and birth-related characteristics data comprise childbirth experience, number of children, diagnosed health problems, prenatal education, self-perceived likelihood of premature birth, level of intention to give birth in the future, and high-risk factors for premature birth.

### Participant Timeline

Recruitment and intervention delivery for participants are structured over 5 cycles. Each recruitment phase spans 2 weeks, during which interested individuals can sign up and immediately complete a preintervention digital survey. After this period, followed by another 2 weeks, an intervention link is sent via SMS text message 3 days prior to commencement (typically on Friday), signaling the start of a 3-week engagement phase according to each participant’s schedule. Throughout the intervention, SMS text messages from research assistant A are sent twice a week (on days 1, 4, 8, 11, 15, and 18) to encourage ongoing participation. The notification schedule is designed to avoid weekends and provide notifications in the middle of the day. A postintervention survey (T1) invitation is sent via text shortly after the intervention ends, with participants expected to complete this survey autonomously within the following week. After a 4-week washout period, a second postintervention survey (T2) follows a similar process. Subsequently, participants are invited to partake in one-on-one qualitative interviews, conducted on the web by 2 researchers. Each recruitment cycle initiates after the completion of the preceding 2-week recruitment phase. A detailed timeline of enrollment, interventions, assessments, and interviews is illustrated in Figure 1.

**Figure 1 figure1:**
[figure not shown]
Time schedule of enrollment, interventions, assessments, and interviews for participants.

### Sample Size

The sample size was calculated using G*Power software (Heinrich Heine University) [30], considering the absence of identical measurement tools and programs for an independent *t* test. A medium effect size of 0.50, a 1-sided significance level of 0.025, a power of 0.80, and an equal allocation ratio (1:1) for the 2 groups were assumed. This analysis determined that a total of 128 participants are required. Given the dropout rates of 20%-40% reported in previous web education program research [31,32], we anticipate a 30% dropout rate. To accommodate this, the study aims to enroll a total of 182 participants, allocating 91 participants to both the experimental and comparative groups, respectively.

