**Methods:**

Using an explanatory sequential mixed methods design, this study first conducts a quantitative analysis followed by a qualitative inquiry to evaluate outcomes and feasibility. Participants are randomly assigned to 2 groups: one accessing the PSIDK-iWebtoons and the other receiving Pregnancy Story I Didn’t Know in Text-Based Information (PSIDK-Texts) over 3 weeks. We measure primary efficacy through the self-management self-efficacy scale for premature birth prevention (PBP), alongside secondary outcomes including perceptions of susceptibility, severity, benefits, and barriers based on the health belief model for PBP and PBP intention. Additional participant-reported outcomes are assessed at baseline, the postintervention time point, and the 4-week follow-up. The feasibility of the intervention is assessed after the end of the 3-week intervention period. Outcome analysis uses repeated measures ANOVA for quantitative data, while qualitative data are explored through content analysis of interviews with 30 participants.

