### Data Analysis

#### Quantitative Data Analysis

The quantitative data collected will be processed using SPSS Statistics (version 25.0; IBM Corp). Descriptive statistics, including frequency, percentage, mean, and SD, will evaluate demographic and pregnancy- and birth-related characteristics. The analysis of primary, secondary, and feasibility outcomes will also include mean, SD, and tests for normal distribution. To compare the homogeneity of characteristics and outcomes (T0) between experimental and comparative groups, chi-square tests and 2-tailed *t* tests will be applied. Depending on the homogeneity of baseline characteristics and initial SMSE-PBP scores, either repeated measures ANOVA or repeated measures analysis of covariance will be used. For nonnormally distributed data, generalized estimating equations will be used. Subgroup analyses based on demographic and pregnancy- and birth-related characteristics (eg, age and education level) will be conducted using linear or logistic regression. The use of the web-based intervention (the number of logins during the intervention period, the number of series completed to the end, and the number of endings collected for each series) in the experimental group will be assessed for primary, secondary, and feasibility outcomes using linear regression analysis. The reliability of measurement tools will be assessed using Cronbach α coefficient, and missing data will be addressed through multiple imputation.

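### The stated 80% power is for a two-group t test, but the primary outcome is to be analysed by repeated measures over three time points with no decisive effect named, so the power figure does not belong to the planned test

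*Protocol article*

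**What the plan says.** The Sample Size section of the protocol article computes the number needed "considering the absence of identical measurement tools and programs for an independent *t* test". The inputs are "A medium effect size of 0.50, a 1-sided significance level of 0.025, a power of 0.80", with 1:1 allocation. The result is 128 participants, raised to 182 for 30% dropout. The section names no time point.

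The primary outcome is the SMSE-PBP. The section on it defines an overall score, the mean of all 60 items on a 1 to 5 scale. It then adds: "Scores for prepregnancy, pregnancy, and hospital phases indicate respective levels of self-management self-efficacy".

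The Participant Timeline sets surveys before the intervention (T0), shortly after the 3-week intervention (T1) and after a further 4 weeks (T2). The abstract gives the same schedule: "Additional participant-reported outcomes are assessed at baseline, the postintervention time point, and the 4-week follow-up".

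Under Quantitative Data Analysis, depending on how well the groups match at baseline, including on initial SMSE-PBP, "either repeated measures ANOVA or repeated measures analysis of covariance will be used". Generalized estimating equations replace these if the data are not normal. The only t tests in that section compare the groups at T0.

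**The concern.** A power statement is useful only for the test that will decide the trial. Here the powered test is a single comparison of two means, and the planned analysis is a longitudinal model that offers several answers.

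- A repeated measures ANOVA over T0, T1 and T2 gives a group main effect. Randomisation makes the expected T0 difference zero, so averaging T0 into this effect dilutes it.
- It also gives a 2-df group-by-time test. That test has no direction, so a one-sided 0.025 level does not map onto it, and a significant result does not say where the groups differ.
- Repeated measures ANCOVA and generalized estimating equations are alternatives chosen after looking at the data.

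The article does not say which of these carries the efficacy claim, or whether T1 or T2 is primary. The same 128 completers can mean quite different power depending on that choice. Leaving it open until analysis also leaves room to choose after seeing results.

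**Working it through.** **Inputs.** From the Sample Size section: d = 0.50, one-sided 0.025, power 0.80, 1:1 allocation, 128 completers (n = 64 per arm). From Participant Timeline and Quantitative Data Analysis: three time points analysed by repeated measures. Two inputs are my assumptions, because the article gives neither. One is a common correlation ρ between time points (compound symmetry) of 0.3, 0.5 or 0.7. The other is the pattern of group differences at T0/T1/T2, either sustained (0, 0.5, 0.5) or halved by T2 (0, 0.5, 0.25).

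**The plan's own figure.** The noncentral t with 64 per arm has noncentrality 0.5 × √(64/2) = 2.83 on 126 df, and power is 0.801. The 128 is reproduced. For dropout, 128/0.70 = 182.9, against 182 stated. The arithmetic is not at issue.

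**Power for the effects the plan could use.** Each uses a noncentral F at 5%, which for a single contrast has the same critical value as one-sided 2.5%. SD is 1 and n/2 = 32.

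1. ANOVA group main effect: λ = 32 × (mean difference)² / [(1 + 2ρ)/3], with 1 and 126 df. The mean difference is 1/3 if sustained and 0.25 if halved. At ρ = 0.3, sustained: 32 × 0.1111/0.5333 = 6.67, power 0.73.
2. Group-by-time: λ = 32 × Σ(difference − mean)² / (1 − ρ), with 2 and 252 df. The sum of squares is 0.1667 if sustained and 0.125 if halved. At ρ = 0.3, sustained: 32 × 0.1667/0.7 = 7.62, power 0.69.
3. T0-adjusted contrast at T1: λ = 32 × 0.25 / (1 − ρ²). At ρ = 0.3: 8/0.91 = 8.79, power 0.84.
4. T0-adjusted average of T1 and T2, which is what repeated measures ANCOVA gives if T0 is the covariate (my reading; the article does not spell it out): λ = 32 × (mean of T1 and T2 differences)² / [(1 + ρ)/2 − ρ²]. At ρ = 0.3, sustained: 8/0.56 = 14.29, power 0.96.

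| Effect tested | Pattern | ρ = 0.3 | ρ = 0.5 | ρ = 0.7 |
|---|---|---|---|---|
| ANOVA group main effect | sustained | 0.73 | 0.63 | 0.55 |
| | halved by T2 | 0.48 | 0.40 | 0.35 |
| Group-by-time, 2 df | sustained | 0.69 | 0.84 | 0.97 |
| | halved by T2 | 0.56 | 0.71 | 0.91 |
| T0-adjusted, T1 only | either | 0.84 | 0.90 | 0.98 |
| T0-adjusted, mean of T1 and T2 | sustained | 0.96 | 0.98 | 0.997 |
| | halved by T2 | 0.80 | 0.85 | 0.94 |

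**Type I error.** One test at 5% has 5% error. If success could be claimed at either T1 or T2, each at two-sided 5% without adjustment, simulation gives 0.095, 0.091 and 0.084 for correlation 0.3, 0.5 and 0.7 (0.0975 if independent).

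**The case against.** The strongest reply is that the mismatch need not cost power. Most of the repeated measures options do better than a plain t test at moderate correlation, and the ANCOVA branch with T0 as covariate reaches at least 0.80 in every case in the table. That stands. A reader might infer from the 0.55 or 0.35 cells that the trial is underpowered, but the article does not support that. Those cells need the ANOVA main effect to be the efficacy test, which the article never says, together with a correlation and an effect pattern it does not give.

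A reader might also infer that the 5% error rate is already lost. That is not supported either. No success rule allowing either time point or any of several scores is stated, and a single omnibus test would not inflate the error.

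Nor is the primary score undefined: the overall item mean is given, and the phase scores are not called co-primary. What remains open is only whether the overall mean alone carries the claim.

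Finally, the decisive effect might be named in a full protocol or analysis plan that is not shown. That could supply the missing choice. It would not alter the fact that this article attaches its power to a test that its own analysis section does not use for efficacy.

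**Conclusion.** The point holds as a mismatch. The 80% belongs to a two-group t test, and the planned analysis is repeated measures ANOVA, ANCOVA or generalized estimating equations over three time points with no decisive effect or time point named. That the t test refers to one time point is an inference from the type of test.

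In the cases worked, power runs from 0.35 to 0.997 around the stated 0.80. This range rests on 64 completers per arm, d = 0.5 at T1, compound symmetry with ρ of 0.3 to 0.7, and the two assumed patterns. The low values come mainly from averaging T0 into a group main effect. The error rate would rise to about 8 to 10% only under an unadjusted either-time-point claim. The sample size itself need not change.

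**What to change.** - Name as primary the between-group difference in the 60-item SMSE-PBP mean at one time point. The choice is the sponsor's; T1, directly after the intervention, is the natural one.
- Always adjust for T0, instead of letting a baseline homogeneity test decide, and test at two-sided 5%.
- Make the other time point and the three phase scores secondary.
- Do not use the ANOVA group main effect that averages in T0 as the efficacy test.
- Restate the power for the chosen contrast. With 128 completers it is at least 0.80 if d = 0.50 at that time point: 0.80 with no T0 correlation, and 0.84 to 0.98 for correlations of 0.3 to 0.7.

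The cost is a few sentences in Outcomes, Sample Size and Quantitative Data Analysis, with no change in enrolment. Trial Status says quantitative data collection ended in March 2024 with analysis expected to finish by October 2024. The choice should therefore be fixed and dated before outcome results are examined by group. If that point has passed, it should be reported openly as a later decision.

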### Recruitment

The recruitment strategy includes using social media platforms such as Twitter, digital forums related to pregnancy or marriage, Kakao open chat rooms, and lifestyle information apps like Daangn Market Inc. Interested individuals will follow the provided web link to read the study details and consent form. The eligibility screening will include questions about gender, age, childbearing intentions, experience with premature birth, and experience working in obstetric clinical settings. Eligible participants will then complete a preintervention survey.

### Allocation

Upon consenting to participate, individuals will receive an alphanumeric identification code from research assistant B, who will also stratify participants by childbirth experience. Allocation sequences will be generated using the “randombetween (1,6)” formula in Microsoft Excel (Microsoft Corp) with 4-block randomization, assigning participants to 1 of 2 groups. Two days before the intervention starts, research assistant A will inform participants of their group’s specific URL. Participants will remain unaware of their group allocation on the first day of the intervention, with the allocation process being managed by research assistant B.

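### The baseline-homogeneity rule in effect keeps the stratification factor, childbirth experience, out of the primary and secondary outcome models, which costs some precision if that factor is prognostic

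*Protocol article*

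**What the plan says.** **Randomisation.** The Allocation section names one stratification factor: research assistant B is the person "who will also stratify participants by childbirth experience". The sequence is generated "with 4-block randomization, assigning participants to 1 of 2 groups". A random draw from 1 to 6 fits a choice among the six orderings of two A and two B.

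**The factor is a baseline characteristic.** In the section on demographic and pregnancy- and birth-related characteristics, "pregnancy- and birth-related characteristics data comprise childbirth experience, number of children" and further items. It is therefore among the variables compared at T0.

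**Analysis.** Quantitative Data Analysis first sets out the comparison of groups at baseline: "To compare the homogeneity of characteristics and outcomes (T0) between experimental and comparative groups, chi-square tests and 2-tailed" t tests. The result selects the model: "Depending on the homogeneity of baseline characteristics and initial SMSE-PBP scores, either repeated measures ANOVA or repeated measures analysis of covariance will be used". The alternative is: "For nonnormally distributed data, generalized estimating equations will be used". Neither sentence names childbirth experience or any other covariate. The subgroup sentence names a class of variables: "Subgroup analyses based on demographic and pregnancy- and birth-related characteristics (eg, age and education level) will be conducted using linear or logistic regression".

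**The concern.** The two sections work against each other. Stratification is meant to prevent imbalance in childbirth experience. The analysis rule makes adjustment depend on imbalance being observed. So the one factor thought important enough to stratify on is the one least likely to lead to adjustment.

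Stratified randomisation removes the between-stratum part of the outcome variance from the true sampling variance of the treatment estimate. A model without the stratum leaves that part in its residual. If the factor is prognostic, the model then reports a larger standard error than the design delivers. What is at stake is precision and power: intervals somewhat too wide and a test below its nominal level. The treatment estimate is not biased, and false positives do not become more likely.

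**Working it through.** **1. The plan's own sample size.** The Sample Size section gives d = 0.50, one-sided alpha 0.025, power 0.80 and 1:1 allocation. With the noncentral t distribution and 64 per group, the noncentrality is 0.50 × √(64/2) = 2.83 and power is 0.8015. The total is 128, as stated. Then 128/0.70 = 182.9, against the stated 182; the difference is immaterial. The checks below use 182 randomised and 128 analysed.

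**2. Can the homogeneity test flag the factor?** Take one continuous sequence of blocks of 4 within each stratum, so the arms differ by at most 2 in a stratum.
- Example: 54 of 182 women have given birth (about 30%, assumed), split 28/26, and the other 128 are split 64/64. The proportions are 28/92 = 0.3043 and 26/90 = 0.2889. Chi-square = 0.01546² / [0.2967 × 0.7033 × (1/92 + 1/90)] = 0.05, against a 5% critical value of 3.84.
- The article describes five recruitment cycles. If blocks restarted at each cycle, the difference in a stratum could not exceed 5 × 2 = 10. With opposite differences of 10 in the two strata and 91 per arm, chi-square = (10/91)² / [0.2087 × 2/91] = 2.63, still below 3.84.
- Simulation with 182 randomised and strata of 20%, 30% or 50% (assumed): the test flagged the factor in 0 of 2,000 trials per scenario. With 30% random dropout it did so in at most 0.1%.

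**3. Single post-intervention score, n = 128.** Let R² be the share of outcome variance explained by childbirth experience. The documents give no value, so a range is shown. The ratio of the reported standard error to the true one is 1/√(1 − R²).

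| R² (assumed) | SE excess | Simulated two-sided size, without term | Simulated power at d = 0.5, without / with term |
|---|---|---|---|
| 0 | 0% | about 0.047 | 0.80-0.81 / 0.80-0.81 |
| 0.05 | 2.6% | 0.046-0.048 | 0.80-0.81 / 0.82 |
| 0.10 | 5.4% | 0.041-0.043 | 0.81-0.82 / 0.84-0.85 |
| 0.20 | 11.8% | 0.029-0.030 | 0.83 / 0.88 |

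The ranges cover strata of 30% and 50%, with 4,000 trials each. With the term, size is about 0.05 throughout. A normal approximation at R² = 0.10 agrees:
- Size without the term: 2 × [1 − Φ(1.96/√0.9)] = 0.039.
- Power with the term: d/√0.9 = 0.527, times √32 = 2.98, and Φ(2.98 − 1.98) = 0.84.
- Power without the term: Φ(2.98 − 1.98/√0.9) = Φ(0.89) = 0.81.

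**4. Group-by-time contrast.** The planned model covers T0, T1 and T2, so the usual treatment test concerns change. Assume a 50% stratum and a total score variance of 1: 0.1 from the stratum, 0.5 between women and 0.4 residual. The baseline-to-post change then has variance 2 × 0.4 = 0.8.
- Stratum effect constant over time: it drops out of the change. The simulated ratio of model SE to true SD was 0.99 with and without the term. A further simulation of 20,000 trials (40% stratum, within-person correlation 0.6, both assumed) gave an unadjusted size of 0.049 at R² = 0.05 and 0.052 at R² = 0.10, which is nominal.
- Stratum effect on change of 0.5 SD: it adds 0.5² × 0.5 × 0.5 = 0.0625 to the variance of change. The expected ratio is √(0.8625/0.8) = 1.038. The simulated ratio was 1.04 without the term and 1.00 with it.

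**The case against.** **The loss is conditional.** A reader might infer that the reported intervals will be too wide. The documents do not support that: they give no association between childbirth experience and the SMSE-PBP score, and at R² = 0 the excess is nil. A reader might also carry the single-score size and power figures over to the primary analysis. That fails too. Women who have given birth may well differ in their level of self-efficacy, but a level difference cancels in a group-by-time test. If the T0 score is a covariate in the ANCOVA, it would also absorb part of such a difference. Both objections stand, so the size is given separately for each scale.

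**The factor is not absent everywhere.** The subgroup regressions cover a class of variables that includes childbirth experience, so it is wrong to say that no stated model can contain it. This stands, and the point is limited to the primary and secondary outcome models.

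**The rule does not strictly exclude it.** The ANCOVA covariates are not listed. Another characteristic might fail its test and trigger ANCOVA, and the list might then include childbirth experience. Differential dropout could also unbalance it among completers. An article may leave a covariate list to the analysis plan. This stands in part: exclusion is nearly certain in effect, not guaranteed. But the article does more than omit a list. It states a rule under which adjustment depends on observed imbalance, and that rule works against the stratified design.

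**Conclusion.** The point holds in a limited form. The stated rule almost never lets the stratification factor prompt adjustment, so the primary and secondary outcome models would in effect be fitted without it. The consequence is conservative inference to the extent that childbirth experience predicts the outcome on the analysed scale.

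On the range considered most relevant, the standard error would be 0% to about 5% too wide for a single score (R² from 0 to 0.10, assumed). For change it would be 0% to about 4% too wide (stratum-by-time effect from 0 to 0.5 SD, assumed). At R² = 0.10 the single-score power given up is about 2 to 3 percentage points. The design still reaches its stated 80% power at 128 analysed. This is minor: a missed gain in precision, not a threat to validity.

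**What to change.** Replace the conditional rule, as far as this factor is concerned, with a fixed statement: childbirth experience (yes/no) is a prespecified factor in the primary and secondary outcome models, whether repeated measures ANOVA, ANCOVA or GEE, regardless of the baseline homogeneity tests. In the repeated-measures models, include its interaction with time as well. A main effect alone would not recover the loss in the group-by-time test. No interaction with treatment is needed for this purpose.

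The cost is one sentence in the plan. With three time points, the model gains one parameter for the factor and two for its interaction with time. The variable is already collected and used for allocation, and the sample size does not change. If the factor turns out not to be prognostic, practically nothing is lost: for a single score, simulated power at R² = 0 was 0.80-0.81 with and without the term.
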